## Methods/Design

### Trial design

DeloRes is a randomized, controlled, observer-blinded multicenter trial with two parallel groups.

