### Outcome measures and definitions

The clinically most relevant parameter in the treatment of full-thickness rectal prolapse is the time to recurrence. Therefore this parameter is defined as primary outcome measure, evaluated during the 24 months following primary surgery. Recurrence is defined as the circular protrusion of rectal mucosa through the anal canal and will be examined by standardized history, clinical examination, and photo documentation. To assess the primary outcome, patients are asked to perform a straining maneuver in a sitting position (patients not able to sit will be assessed in a lateral decubitus position). Then a photograph is taken during straining. The primary outcome is finally determined by the independent review board on the basis of the photograph.

Secondary endpoints are time to and incidence of recurrence of full-thickness rectal prolapse during 5-year follow-up, duration of surgical intervention, morbidity, SAE, all causes of mortality within 3 months after primary surgery (this period was chosen to get any mortality possible related to surgery. Patients with rectal prolapse are usually rather old and frail. There are multiple reasons for further morbidity or mortality which are expected to be unrelated to the surgical procedure in case they occur beyond the first 3 months), length of initial hospital stay, reoperation rate for recurrent prolapse, cumulative hospital stay and change in quality of life, constipation, and fecal incontinence as measured by appropriate questionnaires.

The time to and the incidence of recurrence of full-thickness rectal prolapse during a 5-year follow-up after primary surgery will be assessed as explained above. Morbidity occurring during the primary hospital stay is further differentiated into surgical and non-surgical complications, which are specifically defined as following: severity grading is done with the Clavien classification
[19] and for anastomotic leakage with the classification of the International Study Group of Rectal Cancer
[20]. The definitions of the secondary outcomes are shown in Table 
2. 

**Table 2 T2:** Definitions of secondary outcomes

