### Safety assessments and reporting of adverse events

Analysis of safety-related data is performed with respect to frequency of serious adverse events, frequency of serious adverse events stratified by intensity and causality, and frequency of morbidity in both treatment groups.

From the day of randomization until the regular end of trial follow-up or until premature withdrawal of the patient, all serious adverse events must be documented on a ‘serious adverse event form’ available in the investigator site file.

A serious adverse event will be defined as an event that results in death, is immediately life-threatening, requires or prolongs hospitalization beyond the 20th postoperative day for any medical reason, requires readmission for any medical reason within 3 months after the operation within this trial, requires readmission for treatment of surgical complications related to the study operation beyond 3 months postoperatively, or results in persistent or significant disability or incapacity. Serious adverse events will be classified in intensity (mild, moderate, severe), outcome (recovered completely, recovered with sequelae, not recovered, death, unknown), and causality (unrelated, possibly related, probably related, definitely related, not assessable).

The assessment is based on surgical findings and the clinical course of the patient. It needs to be done by the investigators. Serious adverse events have to be reported by the attending physician to the coordinating investigator or one of both study supervisors within 24 h after the SAE becomes known.

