#### Analysis

The allocation of all patients to the different analysis populations will be defined prior to the analysis (full analysis set (FAS) according to the intention-to-treat principle (ITT; all randomized patients as randomized), per protocol (PP) analysis set, safety analysis set). The procedure of allocation will be documented in the statistical analysis plan. During the data review, deviations from the protocol will be assessed as ‘minor’ or ‘major’. Major deviations from the protocol will lead to the exclusion of a patient from the PP analysis set.

The confirmatory analysis is performed for the full analysis set. The null-hypothesis ‘no difference in the time to recurrence of full-thickness rectal prolapse between experimental and control intervention during the 2-year follow-up after randomization’ is tested by application of the log rank test stratified by center at the two-sided level α=5%. Drop-out and lost-to-follow-up without recurrence of full-thickness rectal prolapse are considered as censoring events.

For the analysis of the secondary outcomes descriptive methods will be used, including the calculation of appropriate summary methods for the empirical distribution as well as calculation of descriptive two-sided *P* values for comparisons of treatment groups. A special focus of the exploratory analyses will be on the time course of the primary as well as the secondary endpoints. Additionally, sensitivity analyses will be conducted for different study populations (per protocol population, appropriate subgroups). Further exploratory analyses will be performed to identify potential prognostic factors for the intervention effect. The time to recurrence of full-thickness rectal prolapse will additionally be analyzed applying a Cox regression model that includes covariates of potential prognostic value.

The safety analysis is based on all randomized patients who were treated with the interventions under investigation. The analysis includes calculation and comparison of the rates of specified complications (see secondary endpoints) and serious adverse events as well as of severity and relationship to intervention and graphical display of the time course. Furthermore, statistical methods are used to assess the quality of data and the homogeneity of intervention groups.

All analyses will be done using SAS version 9.1 or higher.

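### The only stated Clavien grading stops at discharge, so no single severity scale covers complications before and after it, and the dividing point may differ by arm

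*Protocol article*

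**What the plan says.** Two severity scales appear in the protocol article.

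- **Clavien.** In the section Outcome measures and definitions, the sentence that introduces morbidity in the primary hospital stay continues "severity grading is done with the Clavien classification". It adds a separate classification for anastomotic leakage. No Clavien grading is stated for any later period.
- **Intensity.** The section Safety assessments and reporting of adverse events says: "Serious adverse events will be classified in intensity (mild, moderate, severe"). Of the assessment it says "It needs to be done by the investigators". SAEs are recorded from randomization to the end of follow-up.

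Both kinds of data are to be analysed by arm. The safety section lists "frequency of serious adverse events stratified by intensity and causality, and frequency of morbidity in both treatment groups". The Analysis section calculates and compares rates of the specified complications and of "serious adverse events as well as of severity and relationship to intervention".

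**The concern.** The Discussion accepts that fewer recurrences after the abdominal operation may be offset by more morbidity. A reader will therefore want to compare how severe the complications were in each arm, wherever in the postoperative course they arose.

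The plan as written does not give one scale for that. Discharge, which limits the Clavien window, happens after randomization, and length of initial stay is itself a secondary endpoint. If one operation leads to earlier discharge, more of its complications will surface after the Clavien window has closed. A difference between arms in Clavien-graded morbidity could then partly reflect when patients went home, and randomization does not remove that.

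**Working it through.** The plan states no figure on this point, so the check is a comparison of the definitions.

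**Inputs from the protocol article**

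1. Clavien window: the primary hospital stay (Outcome measures and definitions).
2. SAE window: randomization to end of follow-up or withdrawal (Table 2; safety section).
3. SAE criteria that can be met in the primary stay: death, immediate threat to life, a stay beyond postoperative day 20 for a medical reason, lasting disability (safety section).
4. SAE criteria specific to the period after discharge: readmission for any medical reason within 3 months; later readmission for surgical complications of the study operation (safety section).

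**Which scale is stated for which complication**

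| Complication | Clavien | SAE intensity |
|---|---|---|
| Primary stay, not an SAE | yes | no |
| Primary stay, also an SAE | yes | yes |
| After discharge, an SAE | none stated | yes |
| After discharge, not an SAE | none stated | no |

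The first and third rows have no scale in common. Take an intra-abdominal abscess that is treated in the primary stay, is not life-threatening, leaves no lasting disability and is followed by discharge by day 20. It meets none of the criteria in input 3, so it gets a Clavien grade only. If the same abscess appears after discharge and leads to readmission within 3 months, it meets input 4 and only an intensity rating is stated.

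**Effect on the comparison**

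Suppose each arm truly has n complications of a given Clavien grade, and fractions f_D (Delorme) and f_R (resection rectopexy) of them surface before discharge. The Clavien table then shows n·f_D against n·f_R. The apparent difference is n·(f_D − f_R), although the true difference is zero. It vanishes only if f_D = f_R. The intensity table does not recover the loss, because it omits first-row events.

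The article gives no value for n, f_D or f_R, so the size of the difference cannot be calculated. It does make unequal discharge times possible: the Scheme of intervention section leaves fast-track care to each center's own standard, and the Background says that fast-track care speeds discharge. Stratification by center balances center standards between arms, but not a difference in stay caused by the operation itself.

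**The case against.** The strongest reply is that using one scale for surgical morbidity and another for SAE reporting is not a contradiction. SAE recording starts at randomization, so the SAE comparison uses the same scale throughout, and a serious in-hospital complication carries both. This is correct. A reader might infer that every complication changes scale at discharge, or that the SAE comparison itself mixes scales; the text supports neither. What remains is the gap between non-SAE complications in the primary stay and complications at readmission.

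Other stronger readings also fail:

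- **The intensity levels have no definitions.** The article prints none, but it condenses a full protocol and refers to a separate SAE form. Definitions may be there.
- **The raters know the operation.** This is likely, since "The assessment is based on surgical findings and the clinical course of the patient", but it is not stated, and the design is labelled observer-blinded. No blinded Clavien grader is described either, so this does not separate the two scales.
- **SAEs are the only record of harm after discharge.** Table 1 schedules an assessment of complications and safety at every later visit. Intensity is only the sole *severity rating* stated for that period.

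Two further points limit the concern. The Table 2 row on anastomotic leakage carries its own grade and no discharge cut-off, so a late leak may still be graded A to C; the abscess is the cleaner example. The Analysis section's mention of severity may also take in Clavien grades. Even so, no Clavien grade is stated for events after discharge, and the gap stays.

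**Conclusion.** The point holds in this limited form: the stated Clavien grading ends at discharge, the only severity rating stated afterwards is SAE intensity, and for a clinically relevant class of complications the two do not overlap. The split depends on time to discharge, which may differ between the operations.

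This rests on two readings: that the primary-stay limit in the morbidity sentence governs the Clavien grading that follows it, and that a prolonged primary stay counts as an SAE only beyond day 20. Both follow the wording, although the first sentence is loosely punctuated.

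The consequence is confined to comparisons the Analysis section treats as descriptive or as safety. A reader might infer that the trial's main result is at risk. It is not: time to recurrence, the stratified log-rank test, the two-sided 5% level and the 2 x 65 sample size do not use either severity scale. The number of complications affected is unknown.

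**What to change.** 1. **Outcome measures and definitions; Safety assessments.** State that complications after discharge, at least those reported as SAEs, are graded with the Clavien classification already used for the primary stay.
2. **Analysis.** State that complication severity is compared between arms on that grade, pooling events before and after discharge, over a fixed postoperative period that does not depend on discharge. The 3 months already used for mortality and for any-reason readmission is one candidate; the choice is the sponsor's.
3. **Intensity.** Keep the mild/moderate/severe field for SAE reporting only.

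The cost is one extra field on the SAE form, a sentence or so in each section, and retrospective grading of SAEs already reported. The Trial status section gives 34 patients randomized by June 2012, which is 34/130 = 26% of the target, so at that date the retrospective work would have been confined to SAEs in those 34 patients.

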### Statistical methods

#### Sample size calculation

The sample size calculation is based on the analysis of the primary endpoint (time to recurrence of full-thickness rectal prolapse during a 2-year follow-up). A meta-analysis including 17 publications (Delorme
[2,5,6,8,9,12,13,25]; (Laparoscopic) Resection Rectopexy
[1,3,4,7,14,26-28]) showed recurrence rates ranging from 10% to 30% (Delorme’s procedure) and from 0% to 11% (laparoscopic resection rectopexy) (Table 
3). Based on these data, we assume a recurrence rate 2 years after randomization of 20% for the Delorme’s procedure and 5% for resection rectopexy, respectively. If the unstratified two-sided log rank test at level of significance α=5% was applied 2 x 50=100 patients would be required to achieve a power of 1 - beta=80% (nQueryAdvisorR 7.0,
[29]). It is expected that the rate of loss to follow-up without recurrence of full-thickness rectal prolapse will add up to 30%. Even though the lack of information on the primary endpoint at 2 years for these patients is partly addressed by the applied time-to-event method, another 30% of patients will be randomized to compensate for this partial loss of information. It can be expected that application of the center-stratified version of the log rank test will further increase the power. Based on these considerations, a total of 130 patients (2 x 65 patients) will be allocated to the trial which should be sufficient to assure a power of 80% for the confirmatory analysis. 

**Table 3 T3:** Literature review for sample size calculation

**Delorme’s procedure**					
**Author*****et al.***	**Patients (m/f)**	**Study design**	**Recurrences (%)**	**Improvement incontinence %**	**Improvement obstipation %**
Senapati (1994)	32 (8/24)	Retrospective	12.5	41	16
Oliver (1994)	40 (5/35)	Retrospective	22	68	n.s.
Tobin (1994)	49 (6/43)	Prospective	26	50	n.s.
Lechaux (1995)	85 (8/77)	Retrospective	13.5	69	n.s.
Pescatori (1998)	33	Retrospective	21	n.s.	n.s.
Watts (2000)	101 (10/91)	Retrospective	30	89	44
Watkins (2003)	52 (6/46)	Retrospective	10	58	n.s.
Tsunoda (2003)	31 (7/24)	Retrospective	13	63	38
Marchal (2005)	60 (7/53)	Retrospective	23	42	54
**(Laparoscopic) Resection rectopexy**					
**Author*****et al.***	**Patients (m/f)**	**Study design**	**Recurrences (%)**	**Improvement incontinence %**	**Improvement obstipation %**
Huber (1995)	42 (2/40)	Prospective	0	65	41
Stevenson (1998)	30 (1/29)	Prospective	0	70	64
Bruch (1999)	72 (4/68)	Prospective	0	64	76
Kim (1999)	176 (16/160)	Retrospective	5	55	43
Kellokumpu (2000)	34 (3/31)	Prospective	7	n.s.	67
Carpelan (2005)	75 (11/64)	Retrospective	3	n.s.	n.s.
Ashari (2005)	117 (1/116)	Prospective	2.5	62	69
Kariv (2005)	111 (14/97)	Prospective	11	n.s.	n.s.

n.s., Not specified.

#### Analysis

The allocation of all patients to the different analysis populations will be defined prior to the analysis (full analysis set (FAS) according to the intention-to-treat principle (ITT; all randomized patients as randomized), per protocol (PP) analysis set, safety analysis set). The procedure of allocation will be documented in the statistical analysis plan. During the data review, deviations from the protocol will be assessed as ‘minor’ or ‘major’. Major deviations from the protocol will lead to the exclusion of a patient from the PP analysis set.

The confirmatory analysis is performed for the full analysis set. The null-hypothesis ‘no difference in the time to recurrence of full-thickness rectal prolapse between experimental and control intervention during the 2-year follow-up after randomization’ is tested by application of the log rank test stratified by center at the two-sided level α=5%. Drop-out and lost-to-follow-up without recurrence of full-thickness rectal prolapse are considered as censoring events.

For the analysis of the secondary outcomes descriptive methods will be used, including the calculation of appropriate summary methods for the empirical distribution as well as calculation of descriptive two-sided *P* values for comparisons of treatment groups. A special focus of the exploratory analyses will be on the time course of the primary as well as the secondary endpoints. Additionally, sensitivity analyses will be conducted for different study populations (per protocol population, appropriate subgroups). Further exploratory analyses will be performed to identify potential prognostic factors for the intervention effect. The time to recurrence of full-thickness rectal prolapse will additionally be analyzed applying a Cox regression model that includes covariates of potential prognostic value.

The safety analysis is based on all randomized patients who were treated with the interventions under investigation. The analysis includes calculation and comparison of the rates of specified complications (see secondary endpoints) and serious adverse events as well as of severity and relationship to intervention and graphical display of the time course. Furthermore, statistical methods are used to assess the quality of data and the homogeneity of intervention groups.

All analyses will be done using SAS version 9.1 or higher.

### Withdrawals

Participants are allowed to withdraw their written informed consent for the trial at any time and without giving reasons for their decision. If investigators or members of the independent Data Monitoring and Safety Board raise any concerns on an individual patient’s safety, the patient will be withdrawn from the trial.

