***Non-surgical complications***	
Thrombosis	Clinical evidence (for example, pain, swelling, warmth, erythema) of a leg or pelvic vein thrombosis confirmed by duplex sonography or CT angiography, which was not previously known
Pulmonary embolism	Clinical (for example, tachycardia, dyspnea) and/or radiological evidence of pulmonary embolism confirmed by spiral CT or lung perfusion scintigram
Postoperative pulmonary infection	At least three of the following:
	- temperature > 38°C
	- purulent tracheal secretion
	- leucocytes >12 or < 4.5 [10E9/L]
	- elevated CRP
	AND Evidence for pulmonary infection radiologically
Renal failure	Need for dialysis or hemofiltration
Cerebral insult	Ischemic or non-ischemic cerebrovascular event with persistent paresis or paralysis without previous history confirmed by CT or MRT
Myocardial infarction	Electrocardiogram (NSTEMI or STEMI) and enzyme (Troponin I) changes suggestive of myocardial infarction or needing admission to coronary care unit
*Serious adverse events*	SAE occurring from the day of randomization until regular end of trial follow-up or withdrawal
*Mortality*	All causes of mortality within 3 months after primary surgery
*Duration of surgical intervention*	First incision to the completion of skin closure (resection rectopexy) or the last coloanal suture (Delorme’s procedure)
*Length of initial hospital stay*	Means the hospitalization period from the primary operation date until the day of discharge (= postoperative hospital stay)
*Reoperation rate for recurrent prolapse*	Any surgical intervention for a recurrence
*Cumulative hospital stay*	Defined by the days in hospital after the primary surgery as well as the following hospitalizations due to complications or recurrence within 24 months after the primary operation
*Change of quality of life, constipation and incontinence*	
	Measured by means of the appropriate questionnaires SF-12, ( [22], validated in German), Herold constipation score ( [23], evaluated in German, but not yet published), Wexner-Score ( [10], non-validated in German, most commonly used score) and Rockwood-FIQLScore ( [24], validated), prior to the surgical intervention as well as 6, 12, and 24 months after the intervention

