### Compliance/rate of loss to follow-up

To reduce the number of patients not able or willing to visit the study centers a study nurse will be appointed to visit the patients and to assess the outcome at the specified time (‘flying study-nurse’). Furthermore, the time-to-event method will be applied for the primary analysis to allow for all available information including the observation time of patients who drop out early. Nevertheless, an additional percentage of patients will be recruited to assure a sufficient power for the confirmatory analysis.

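### Withdrawing a patient from the trial for any safety concern ends SAE recording after a single operation, so later harms are lost; recurrence data may be lost too

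*Protocol article*

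**What the plan says.** Protocol article, Withdrawals: if an investigator or a member of the safety board has a concern of any kind about the safety of a patient, "the patient will be withdrawn from the trial". The rule is mandatory, has no threshold, and refers to the trial rather than to a treatment.

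Protocol article, Safety assessments and reporting of adverse events: SAEs are documented from randomization "until the regular end of trial follow-up or until premature withdrawal of the patient". Table 2 puts the same limit into the outcome definition: "SAE occurring from the day of randomization until regular end of trial follow-up or withdrawal".

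Protocol article, Analysis: "Drop-out and lost-to-follow-up without recurrence of full-thickness rectal prolapse are considered as censoring events". The section on compliance and loss to follow-up says that the time-to-event method uses all available information, "including the observation time of patients who drop out early". On the analysis population: "The confirmatory analysis is performed for the full analysis set", which is defined as all randomized patients as randomized.

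Nothing in the article keeps a patient withdrawn for safety under observation for recurrence, SAEs or death.

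**The concern.** Withdrawal from a trial can protect a patient when there is continuing trial treatment to stop. Here Table 1 shows the intervention at one visit only. After that visit, taking the patient out of the trial leaves the exposure as it was and stops the recording of its consequences.

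The trigger is also close to the outcomes being compared. The safety board periodically reviews potentially related SAEs, and the SAE definition includes prolonged stay and readmission for surgical complications. A patient with one serious complication is a likely subject of a safety concern and also a likely source of further events.

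Two things are at stake. The first is the safety comparison, which the Discussion treats as capable of outweighing fewer recurrences. The second, on a further assumption, is the primary log-rank test, which needs censoring to be unrelated to recurrence risk.

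**Working it through.** **1. SAE data (no arithmetic needed).** The chain is stated in full: any safety concern leads to withdrawal, and withdrawal ends SAE recording. If the triggering event is itself an SAE, it is counted. What is lost is every later event in that patient, with its intensity, causality and outcome. Death is an SAE, so later deaths also leave this reporting route. The 3-month mortality endpoint in Table 2 has no withdrawal limit of its own, so its loss is possible but not stated. If the arms differ in how often the rule is triggered, the arm with more triggers has more of its SAEs cut off. No link to recurrence is needed for this.

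**2. Recurrence data (one inferred step).** That recurrence assessment stops is not written word for word. It follows from withdrawal being from the trial, and from drop-outs contributing only their time up to drop-out and then being censored.

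**3. Expected events.** Inputs from Sample size calculation: 65 per arm, 2-year recurrence 20% and 5%, 30% loss without recurrence.

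- No loss: 65 × 0.20 + 65 × 0.05 = 13 + 3.25 = 16.25 events.
- With 30% loss, exponential times assumed: λ₁ = −ln(0.80)/2 = 0.112, λ₂ = −ln(0.95)/2 = 0.026, μ = −ln(0.70)/2 = 0.178 per year. Events per arm = 65 × λ/(λ+μ) × (1 − e^(−2(λ+μ))), giving 11.0 + 2.7 = 13.7.
- If recurrences are seen only at months 6, 12 and 24 (simulated): about 12.9.

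Losing 10% of Delorme recurrences is therefore about one event (0.10 × 11.0 = 1.1), and 20% about two.

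**4. The plan's own figure.** The 100 × 1.3 = 130 step reproduces. The 2 × 50 before it does not: HR = ln 0.95 / ln 0.80 = 0.23, Schoenfeld events = 4(1.960 + 0.842)²/(ln 0.23)² = 14.5, and 14.5/0.125 = 116, or 58 per arm. That is a separate matter and this point does not rest on it, but it explains why the baseline power below is under 80%.

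**5. Illustration for the primary test.** The document gives no frequency of safety withdrawals, so the shares are assumptions. Simulation: 65 per arm, 30% exponential loss, unstratified log-rank test, detection at 6, 12 and 24 months, and the given share of would-be recurrences censored at the preceding visit. Figures are rounded; repeat runs agree within about one percentage point.

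| Share of recurrences lost | Power, lost in both arms | Power, lost in Delorme arm only | Type I error, lost in one arm (12.5% true rate in both) |
|---|---|---|---|
| 0% | 66% | 66% | 4.9% |
| 5% | 64% | 62% | 5.1–5.4% |
| 10% | 61% | 57% | 5.2–5.5% |
| 20% | 56–57% | 48% | 6.2–6.6% |
| 30% | not run | not run | 8.2–8.5% |
| 40% | not run | not run | 11.3–11.8% |

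Loss in the Delorme arm only pulls the hazard ratio toward 1. At 10%, the Delorme rate is seen as 18% and HR = ln 0.95 / ln 0.82 = 0.26 instead of 0.23. Loss in the rectopexy arm only would move it the other way.

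**The case against.** The article condenses a full protocol, and what is collected after withdrawal could be spelled out there. Other parts of the article assume that patients with complications stay in: Table 1 schedules safety assessment to month 60, late readmissions for surgical complications are SAEs, and cumulative hospital stay counts later admissions to 24 months. This suggests that the authors did not mean every complication to end participation. Randomization is 24 to 48 hours before surgery, so the clause may also act before the operation, where the argument about exposure does not apply. These points weaken any claim about how often the rule would be used. They do not remove it: the rule is stated affirmatively, and two other places tie SAE recording to it.

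A reader might infer more than the text supports:

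- *That the rule builds informative censoring into the primary test.* Nothing in the article links safety concerns to later recurrence. The listed complications are perioperative or medical. Without such a link, the withdrawals cost information but do not bias the test.
- *That it falls on exactly the patients whose repair is failing.* Only drop-out without recurrence is censored, so a recurrence documented before withdrawal counts.
- *That it defeats the full analysis set.* Withdrawn patients remain in it as randomized, with their time at risk.
- *That unblinded investigators drive it.* Safety board members can also trigger it, the article does not say whether the investigators concerned are blinded, and an independent board judges recurrence from photographs.
- *That the missing sensitivity analysis for censoring is an error.* That may stand in the statistical analysis plan, which is not shown.

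**Conclusion.** The point holds as a defect in a stated rule. Followed as written, it cuts off SAE data, and possibly mortality data, in the patients most likely to have further events, without removing any exposure once surgery is done. This is the direct and supported harm. It also works against the article's own aim, under the exclusion criteria, of limiting attrition bias.

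The effect on the primary test is conditional. It needs recurrence assessment to stop at withdrawal (implied) and, for bias rather than lost information, a relation between safety concerns and recurrence (plausible, not documented). Neither size nor direction can be derived from the document. At assumed shares of 5–10% lost in one arm, type I error stays at or below about 5.5%, and power falls by roughly 4 to 9 points if that arm is Delorme. Clear inflation of type I error needs 20% or more, for which the document gives no basis.

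**What to change.** In Withdrawals, in the safety section and in the SAE row of Table 2, separate clinical safety decisions from study follow-up. For example: *a safety concern does not by itself end data collection; recurrence, SAE and mortality data continue at the scheduled visits to months 24 and 60 unless the patient withdraws consent to this.* The criteria for clinical safety decisions stay as they are. A sensitivity analysis for safety-related censoring is optional and can go in the statistical analysis plan.

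The cost is a change of wording in three places. The retained patients use visits, and the travelling study nurse, that are already planned. As of June 2012, 34 of 130 patients had been randomized, so 96 were still to come. Recruitment began in September 2010, 21 months earlier, so no patient could yet have reached month 24. An analysis plan alone cannot make the repair, because it cannot recover events that were never recorded.
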